***Research design and recruitment.*** A mixed-methods study, including a cross-over RCT, and semi-structured focus groups, alongside economic evaluation, will be conducted. A Cross-over design will be adopted to minimize the effect of confounders and inter-individual variability (because each participant serves as their own control)^27^ and encourage participant enrolment in the trial.^28^ A mixed-methods approach will be considered because the combination of qualitative and quantitative methods can contribute to interdisciplinary and comprehensive research evidence.^29^ This trial will include: (1) a two-step screening phase for eligibility; (2) a baseline assessment (time-point [T1]); (3) 12 weeks of supervised treadmill training for the HIAT group; (4) post-treatment outcome assessments and economic evaluations at 12 weeks (T2); (5) a washout period for four weeks, followed by the cross-over of HIAT and WLC groups; (6) 12 weeks of supervised treadmill training for the WLC group; (7) outcome assessments at 28 weeks (T3); and (8) semi-structured focus groups at 32 weeks. Potential participants will be recruited via advertisements (study flyer) distributed at the Hong Kong Polytechnic University and the Education University of Hong Kong (please see upport letter) campuses and throughout the local community and by word-of-mouth.

***Sample size:*** G-Power analysis^30^ (3.1.9.2), set for an F-test (analysis of variance (ANOVA), was used to estimate the sample size required to reliably test the study hypotheses. We will enrol 130 participants (65 per group), allowing for a 30% attrition rate (the drop-out rate in our previous RCT^9^ with a seven-month follow-up was 20%–23%). For Hypothesis 1, the estimated sample size was 86 (43 per group). The power was set to 90%, the alpha level was 0.05, the drop-out rate was 30%, and effect-size was 0.60 (from our previous RCT^9^). For Hypothesis 2, based on estimated changes in progesterone levels from our pilot trial (***d*** = 0.36),^13^ the sample size required to detect differences in progesterone with 90% power at the 5% significance level is 100 (50 per group). Assuming a 30% drop-out rate, 130 participants (65 per group) would be required.

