***Hypothesis 2.*** The mediation effects of increased progesterone levels on pain will be assessed using the Sobel test.^51^ A four-step model using linear regression will be tested. In Step 1, the regression coefficient between prostaglandin levels and pain (Path C) will be estimated. In Step 2, the regression coefficient between progesterone and prostaglandin levels (Path A) will be estimated. In Step 3, the regression coefficient between pain and prostaglandin levels, along with the mediator, progesterone levels (Path B), will be evaluated. Step 4: the Sobel test will be used to estimate the standard error of Path AB using the formula B^2^SA^2^ + A^2^SB^2^, where A and B are the regression coefficients of Paths A and B, respectively, and SA and SB are the standard errors of Paths A and B, respectively.^51^ The online Sobel test calculator (<http://quantpsy.org/sobel/sobel.htm>) will be used. Hypothesis 2 will be supported if the Sobel test indicates a significant (p < 0.05) mediation effect.

***Hypothesis 3***. The unadjusted mean costs and cost differences between HIAT and the usual care groups for total and disaggregated costs (intervention costs, healthcare utilisation costs, including healthcare services and medications utilised, and absenteeism costs) will be calculated.^48^ The seemingly unrelated regression (SUR) analyses will be used to estimate the total cost differences (ΔC) and effect differences (ΔE). The SUR analyses will be performed by adjusting for baseline demographic and health characteristics (such as pain intensity and menstrual-cycle length or the number of bleeding days) between groups.^48, 52^ The advantage of SUR is that two regression equations, one for ΔC and one for ΔE, are modelled simultaneously allowing possible correlations between cost and outcome differences to be accounted for.^48, 53^

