The EQ-5D responses will be converted into utility scores to estimate the gain or loss of quality-adjusted life-years (QUALYs). The incremental cost-effectiveness ratio (ICER) will be calculated using the formula ICER = ΔC / ΔE. The advantage of this approach is that our confidence intervals do not rely on the usual normality assumption. Uncertainty surrounding the ICERs and the 95% confidence intervals around cost differences will be estimated using bias-corrected and accelerated bootstrapping with 5,000 replications.^48^ The cost-effectiveness of the intervention groups will be geographically represented using the cost-effectiveness plane (CE). The threshold (λ) for cost-effectiveness or the amount of money the country is willing to pay to gain one unit of effect (QALY) will be calculated.

Further, we will determine whether the intervention is cost-effective by utilising two other thresholds to test the robustness of our conclusion: (1) GDP per capita (in terms of purchasing-power parity), which is the threshold suggested by the World Health Organisation Commission for Macroeconomics and Health for an intervention to be ‘very cost-effective’;^54^ and (2) the country-specific thresholds published by Woods et al.,^55^ based on extrapolating the opportunity costs of healthcare spending in the United Kingdom. The cost-effectiveness acceptability curve (CEAC) will be derived based on the λ value. Using the CEAC, the cost-effective treatment options will be predicted based on the different λ levels. A secondary analysis will be performed from a healthcare perspective by excluding absenteeism costs.^48^ The robustness of the primary analysis will be tested using the following two sensitivity analyses: (1) repetition of the analysis including completed participants alone; and (2) excluding cost-outliers or data from participants with extremely high absenteeism costs.^48^ Hypothesis 3 will be supported if HIAT yields cost (direct and indirect) savings and results in lower healthcare utility compared with WLC receiving usual care at assessment T2.

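### The Sobel test that alone decides Hypothesis 2 is conservative when the mediation paths are small to moderate, and a bootstrap interval or joint-significance test would recover up to about 20 points of power

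*Protocol*

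**What the plan says.** Under the Hypothesis 2 heading of the statistical section, the protocol fixes the test ("The mediation effects of increased progesterone levels on pain will be assessed using the Sobel test"), the tool ("The online Sobel test calculator") and the decision rule: "Hypothesis 2 will be supported if the Sobel test indicates a significant (p < 0.05) mediation effect".

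The product being tested is built from two regressions. For the first, "the regression coefficient between progesterone and prostaglandin levels (Path A) will be estimated". For the second, "the regression coefficient between pain and prostaglandin levels, along with the mediator, progesterone levels (Path B), will be evaluated".

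No bootstrap, product-distribution interval or joint-significance test is named for the indirect effect. A bootstrap does appear under Hypothesis 3 ("bias-corrected and accelerated bootstrapping with 5,000 replications"), but only for costs and cost-effectiveness ratios.

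The sample size paragraph plans Hypothesis 2 on a difference in progesterone (pilot d = 0.36; 100 participants, enrolled as 130 for 30% drop-out). It states no size for Path A or Path B.

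**The concern.** A p-value below 0.05 should occur about 5% of the time when there is no mediation. The Sobel statistic is compared with a normal curve, but the product of two estimates is not normal when the true paths are small relative to their standard errors. The statistic then reaches 1.96 too rarely.

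Because this one p-value decides Hypothesis 2, a real mediated effect could be missed more often than the data require. A non-significant result could then be misread as evidence against the progesterone-prostaglandin mechanism. The test and the rule are both written into the protocol, so this is not a detail left to a later analysis plan.

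**Working it through.** **The plan's own figure.** The protocol gives no size or power for the mediation test, so there is none to reproduce. The stated 100 participants concern a progesterone difference. A plain two-group comparison with d = 0.36, 90% power and two-sided 5% needs 163 per group. About 100 in total arises only from a repeated-measures F-test with an unstated correlation. That is a separate matter and is not used below.

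**Inputs.** From the protocol: 5% level (two-sided assumed, since sidedness is not stated), n = 130 enrolled, n = 100 stated as required, and 130 × 0.70 = 91 completers. Assumed: the path sizes, one observation per participant, and normal errors. The correct standard error, with the square root, is used throughout; the printed expression is the variance.

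**Why the test is conservative.** Write zA = A/SA and zB = B/SB. Then

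Sobel z = AB / √(B²SA² + A²SB²) = zA·zB / √(zA² + zB²).

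So 1/z² = 1/zA² + 1/zB², and the Sobel z is always smaller in size than the weaker of the two path statistics. If both are equal, each must reach 1.96 × √2 = 2.77. If one is very large, Sobel z approaches the other and the test behaves normally.

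**Size, approximate hand check at n = 100.** Let one path be zero and the other a correlation r, with expected statistic r√98 / √(1 − r²).

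- r = 0.3: statistic 3.11. The null path must exceed 1/√(1/1.96² − 1/3.11²) = 2.52, which has probability about 1.2%.
- r = 0.5: statistic 5.72. The null path must exceed 2.09, probability about 3.7%.

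**Size, simulated (n = 100, 40,000 trials each):**

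| Non-zero path | 0.1 | 0.2 | 0.3 | 0.4 | 0.5 | 0.6 | 0.8 |
|---|---|---|---|---|---|---|---|
| Sobel | 0.07% | 0.4% | 1.3% | 2.5% | 3.8% | 4.3% | 4.9% |

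In separate runs of 1,500 trials with one path zero and the other 0.30, the percentile bootstrap gave 4.4% and Sobel 1.9%. With both paths zero, Sobel gave 0.005% to 0.02%, and the comparators were also only about 0.1% to 0.2%.

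**Power, Sobel v percentile bootstrap** (1,500 to 2,000 trials, 1,000 resamples):

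| n | Paths | Sobel | Bootstrap |
|---|---|---|---|
| 91 | both 0.25 | 21% | 41% |
| 91 | both 0.30 | 48% | 65% |
| 91 | both 0.35 | 69% | 82% |
| 100 | both 0.25 | 28% | 49% |
| 100 | both 0.28 | 43% | 62% |
| 100 | 0.18 and 0.30 | 19% | 35% |
| 130 | both 0.20 | 18% | 38% |
| 130 | both 0.25 | 45% | 65% |
| 130 | both 0.30 | 74% | 85% |

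Against joint significance (both paths individually significant), the largest gap over a grid of path sizes was 21.6 points at n = 91 (35% v 57%), 21.5 at n = 100 (32% v 53%) and 22.3 at n = 130 (27% v 49%).

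**Where the loss fades.** At n = 100 with both paths 0.39 the gap is 6 to 7 points when paths are scaled with unit error variance. A repeat run of 20,000 trials with both paths as correlations gave 4.5 points. At 0.5 the gap is under 1 point on either scale.

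**The case against.** Sobel is an established, prespecified test and its error is on the safe side. Several stronger readings are tempting, and the protocol does not support them.

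- *The size is far below 5% whatever the variables.* It is not. Path strength decides, and with one path at 0.5 or more the size is about 4% to 5%. The background section describes an inverse, regulatory link between progesterone and prostaglandin, so a strong Path A cannot be excluded.
- *A size near zero with both paths zero shows the defect.* It does not, because every comparator is also far below 5% there. The deficit specific to Sobel appears when one path is non-zero.
- *The pilot d = 0.36 shows that the paths are small.* It is a group difference in progesterone, and neither regression contains treatment. If it is used anyway as a treatment path, 0.36/√(0.36² + 4) is about 0.18. At n = 91 with a second path of 0.2 to 0.6, the gap is then 5 to 14 points and bootstrap power never exceeds about 44%. On that reading sample size is the larger problem, and changing the test would not remove the risk of an uninformative null.
- *The Hypothesis 3 bootstrap contradicts this choice.* It serves a different quantity. It shows only that the team already plans to bootstrap.

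Two further cautions stand. The percentile bootstrap can be mildly liberal, at about 6% to 7% for n near 91 with one path at 0.5 to 0.7 and the other zero. The simulations also model neither the cross-over repeats nor the planned group-mean imputation. None of this removes the loss of power when the paths are small to moderate.

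**Conclusion.** The point holds as a matter of efficiency. For standardised paths of about 0.4 or less, the sole criterion for Hypothesis 2 runs well under its nominal 5% level. Over assumed path sizes it gives up at most about 20 points of power to tests that are just as easy to apply. That figure is a maximum, not a prediction for this trial: the protocol supplies no path sizes, and the loss largely disappears when the paths are strong.

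A reader might infer that the test is invalid or produces false positives. It does not, because the Sobel z can never exceed the weaker path statistic. The change is worth making because it is cheap, but it ranks below defining which indirect effect is to be tested.

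**What to change.** First settle the regressions. As written they contain no treatment term, so neither the indirect effect of the exercise programme nor its expected sign is defined. Changing the test does not cure this.

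Then replace the Hypothesis 2 decision rule with wording such as:

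> Hypothesis 2 will be supported if the two-sided 95% percentile bootstrap confidence interval for the indirect effect (5,000 resamples of participants, fixed seed) excludes zero in the hypothesised direction. The Sobel statistic will be reported descriptively.

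The cost is a change of wording and a few minutes of computing, with no extra participants or data. The online calculator will no longer suffice. The possible mild liberality near n = 91 should be acknowledged. If that is unwelcome, requiring both paths to be individually significant is an alternative with nearly the same power: at n = 130 with both paths 0.25, 65.7% against 64.8% for the bootstrap and 45.2% for Sobel.

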***Saliva collection*.** Saliva will be collected as described in a previous study.^35^ All participants will receive salivary kits and specimen bag with participant details [name, PIN and group allocation]) and written instructions for saliva collection procedures. The RA will provide training to all participants for the collection of citric-acid stimulated saliva (approximately 5 mL). In our recent pilot trial, mediators levels were evaluated in plasma; however, in the current proposed study, these mediators will be measured in saliva. Some participants from our recent pilot trial, in which we collected plasma for the estimation of mediator levels,^13^ reported a preference for non-invasive diagnostic tests over invasive tests (blood collection) and expressed difficulty reporting to PolyU for blood collection when their menstrual periods started on weekends. Additionally, the circulating levels of PGF_2α_ in peripheral plasma are commonly very low because PGF_2α_ is inactivated during its initial entry through the lungs.^36^ Studies have reported that salivary measures provide a reliable and non-invasive method for assessing progesterone^37^ and prostaglandins.^35^ The home collection of saliva is convenient and cost-effective and can be done easily and safely without assistance.^38^ Therefore, for the current proposed study, mediators concentrations will be measured in the saliva, instead of blood plasma. Participants will be instructed to collect saliva immediately after the start of menstruation and two hours following the start of menstruation, to store samples in a freezer.^35^ The RA will transport the samples to the lab for further processing.

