**Statistical tests and anticipated results**

*Missing data and data preparation*. We will implement strategies, such as the digital diary, follow-up phone-call reminders, and providing routine encouragement to continue exercise, to minimise missing data. Missing values will be replaced with group means. All statistical analyses will be performed on an intention-to-treat basis, using SPSS (version 24).

***Hypothesis 1.*** The two phases that each participant completes during the course of a cross-over trial are typically referred to as the two study periods.^49^ First, a preliminary test will be carried to rule out carryover effects and to test our study for validity.^50^ This will be performed by estimating the sum of the values measured during the two treatment periods for each participant and compared across the groups by using an independent samples *t*-test.^49^ Second, the within-participant differences in outcome variables between the study periods will be calculated using a two-sided Student’s unpaired *t*-test.^49, 50^ Treatment effects will be evaluated using an ANOVA with a mixed-effects model considering the longitudinal repeated measures, including the effects of time (T1, T2, and T3) within each study group and the interaction between time and intervention. Post hoc analysis using the Bonferroni correction will be performed. Hypothesis 1 will be supported if significant reductions in pain intensity and university absenteeism and a significant improvement in academic performance are reported following 12 weeks of HIAT compared with baseline measurements.

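### The Hypothesis 2 mediation is specified as plain linear regression of levels, with no participant, period or treatment term, on data that repeat within women in a cross-over

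*Protocol*

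**What the plan says.** The Hypothesis 2 paragraph of the protocol (Statistical tests and anticipated results) sets out the mediation in some detail:

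- Model: "A four-step model using linear regression will be tested".
- Step 2: "the regression coefficient between progesterone and prostaglandin levels (Path A) will be estimated".
- Step 3: "the regression coefficient between pain and prostaglandin levels, along with the mediator, progesterone levels (Path B), will be evaluated".
- Step 4: the two coefficients and their standard errors go into a Sobel calculation, made with "The online Sobel test calculator".
- Success rule: "Hypothesis 2 will be supported if the Sobel test indicates a significant (p < 0.05) mediation effect".

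No participant, period, visit or treatment term is named, and the variables are described as levels.

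The data behind these regressions are repeated. On saliva (Saliva collection): "Participants will be instructed to collect saliva immediately after the start of menstruation and two hours following the start of menstruation". On visits, the Hypothesis 1 model is described as "including the effects of time (T1, T2, and T3) within each study group", and it is a mixed-effects repeated-measures model. On design (Research design and recruitment): "A Cross-over design will be adopted to minimize the effect of confounders and inter-individual variability". So Hypothesis 1 gets a model that respects the repeated measures, and Hypothesis 2 does not.

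**The concern.** Hypothesis 2 is about change within a woman: HIAT raises her progesterone, her PGF2α falls and her pain falls. A regression of levels with no participant term does not isolate that change. Two readings of the text cause trouble, in different ways.

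- **Rows pooled.** A woman can contribute three visit rows, or six if both saliva samples are entered. Ordinary regression treats them as independent, so the standard errors of Paths A and B are too small and the Sobel statistic too large.
- **One visit used.** The rows are independent, but the paths become correlations between women. A woman with a stably different hormone level and a stably different pain sensitivity looks like evidence of mechanism. This is the inter-individual variability that the cross-over was chosen to remove.

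At stake is the mechanistic claim of the trial, which is accepted on a single p-value below 0.05. The issue is separate from which variable is placed as predictor or mediator, and it would remain after any correction of that order.

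**Working it through.** **Inputs from the protocol.** 130 women and 30% drop-out, so 130 × 0.70 = 91 completers; three time-points; two saliva samples per menstruation; nominal alpha 0.05, taken as two-sided. The plan gives no error rate for the mediation test beyond the nominal 5%, so there is no figure of its own to reproduce.

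**Assumptions, not in the protocol.** Intraclass correlation (ICC) of each variable across visits: 0.3, 0.5, 0.7. Share of within-woman variance common to the two samples of a visit: 0.7. The non-zero path is 0.3 to 0.5.

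**Test.** z = AB / √(B²SA² + A²SB²), positive if |z| > 1.96. There is no mediation if either path is zero.

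**Step 1: pooled rows, by formula.** For a slope between two clustered variables, the true variance exceeds the ordinary regression variance by

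D = 1 + Σ (predictor correlation × outcome correlation), summed over the woman's other rows.

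A nominal 5% test of that path then rejects with probability 2[1 − Φ(1.96/√D)]. The Sobel test approaches this rate when the other path is clearly non-zero, and otherwise generally lies below it.

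*Three visit rows:* D = 1 + 2·ICC².

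*Six sample rows:* the same pain score is attached to both samples of a visit (outcome correlation 1), the predictor correlation within a visit is ICC + 0.7(1 − ICC), and four rows come from other visits. So D = 1 + [ICC + 0.7(1 − ICC)] + 4·ICC².

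| ICC | D, three rows | Rate | D, six rows | Rate |
|---|---|---|---|---|
| 0.3 | 1.18 | 7% | 1 + 0.79 + 0.36 = 2.15 | 18% |
| 0.5 | 1.50 | 11% | 1 + 0.85 + 1.00 = 2.85 | 25% |
| 0.7 | 1.98 | 16% | 1 + 0.91 + 1.96 = 3.87 | 32% |

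**Step 2: pooled rows, Sobel test simulated** (ICC 0.3 / 0.5 / 0.7).

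- Path B = 0, Path A 0.3-0.5, 100 women: three rows 5-7 / 9-10 / 13-16%; six rows 16-17 / 23-24 / 30-31%.
- Path A = 0, Path B = 0.5, 91 women: three rows about 8 / 10 / 18%; six rows about 15 / 18 / 26%.
- Both paths zero: at most about 4%, even with six rows.

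For 91 to 130 women (ICC 0.5, Path A 0.3) the rates hardly move: 23-24% for six rows and 9-10% for three.

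**Step 3: one visit, one row per woman.** With no shared stable traits the rate is at most about 4%. If the three variables are linked only through stable woman-level traits, with between-woman correlation r and no within-woman relation (91 women, ICC 0.3 / 0.5 / 0.7):

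| r | One visit | Three visits pooled |
|---|---|---|
| 0.2 | at most 1.4% | 0.6 / 5 / 19% |
| 0.3 | 0.3 / 1 / 6% | 3 / 22 / 53% |
| 0.5 | 1 / 14 / 49% | 21 / 77 / 95% |

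**Step 4: within-woman differences.** Regressing T2 minus T3 differences gives under 0.1% in the r = 0.5 trait scenario, because stable traits cancel, and about 3% with Path A = 0 and ICC 0.5.

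Differences alone are not enough, because HIAT itself moves the variables together. If HIAT shifts each of the three by 0.6 SD independently, with no mediation, the difference regression is positive in 5 / 16 / 61% of trials. Adding sequence group as a covariate brings this to about 0%. A participant-and-period model without a treatment term has the same weakness: 14% at ICC 0.5 with shifts of 0.35, 0.36 and 0.60 SD and a true Path A of 0.3.

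**The case against.** The strongest reply is that the protocol never says rows will be pooled. Choice of visit, handling of duplicate samples, and levels versus changes are often settled in a statistical analysis plan, which is not shown here. Linear regression on within-woman changes gives one row per woman, keeps the within-woman contrast and is still linear regression. The hypothesis itself speaks of increased progesterone and improved pain, which leans that way. Even the two-sample, three-visit structure is partly inferred: saliva is stated expressly for baseline and only implied at T2 and T3.

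Most of this stands. A reader might infer that the protocol treats repeated values as independent, that pooling and discarding the cross-over are the only two possibilities, or that false mediation rises whichever rows are used. The document supports none of these. Pooling is one reading, regression on changes is a third option, and a single-visit Sobel test is conservative unless stable traits are shared. The largest figures need r = 0.5, an undocumented value; at r = 0.3 the one-visit rate stays at 6% or below.

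The reply does not remove the point. The paragraph is not merely silent. It fixes the model, the paths, the variables as levels, the standard-error formula, the calculator and the success rule, with no term for participant, period or treatment. An analysis plan that follows it literally inherits the problem. Even the favourable reading, regression on changes, lacks the treatment term that Step 4 shows to be needed.

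**Conclusion.** The concern holds in a limited form. The specified regressions do not reflect the cross-over: they have no participant, period or treatment term, and the rows that enter are undefined.

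- Pooled rows: roughly 5-18% (three visits) or 15-31% (six rows) false positives against 5%, for assumed ICCs of 0.3-0.7 and one non-zero path.
- One visit: no inflation in itself (at most about 4%), but exposure to stable between-woman confounding, at 0.3-6% for r = 0.3 and 1-49% for r = 0.5.

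The direction is secure. The size rests on ICC, path and between-woman correlation values that the protocol does not give. The missing participant and treatment terms matter much more than the missing period term: a shift of 0.2 SD per visit moved the pooled rates only to 24.6% (six rows) and 10.8% (three rows) at ICC 0.5. The plan should be changed, since a better-suited analysis of the same data is available at little cost. It is not shown that the trial would in fact report false mediation.

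**What to change.** Amend the Hypothesis 2 paragraph as follows.

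1. Average the two saliva samples of each visit, or name the one that is used.
2. Fit every mediation regression on within-participant T2 minus T3 differences, one row per woman, with sequence group as a covariate. The intercept and the sequence term then carry the period and treatment effects. Alternatively, use a mixed model with participant, period and treatment terms and within-woman centred mediators. The two need not agree exactly if T1 enters the mixed model, so name one as the main analysis.
3. Take standard errors, or a bootstrap interval for the indirect effect, at participant level. The Sobel calculator can stay if it is given participant-level standard errors; six rows with participant-clustered errors gave about 3% in simulation (ICC 0.5, Path A 0.3). Clustering alone does not remove confounding by stable traits or by treatment, so it does not replace item 2.

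The cost is rewording, slightly more analysis work, and some loss of precision because between-woman information is set aside. No new data are needed.

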**Background of Research**

*Prevalence and impacts of dysmenorrhea****.*** Primary dysmenorrhea is a debilitating condition that affects nearly half of all menstruating women worldwide.^1^ A cross-sectional survey performed in 2013 in Hong Kong (HK) found that out of 240 18–25-year-old female university students, the prevalence of dysmenorrhea was 80%.^2^ Primary dysmenorrhea has been linked to regular educational absenteeism,^3^ and the class attendance rate among women has been reported to decrease by 29%–50% during menstruation.^4^ Recurrent absenteeism has negative impacts on young women, decreasing the total contact time for learning, which may affect the quality of the educations they receive.^3^ Studies that have examined the impacts of primary dysmenorrhea on daily life have reported that adolescent women with primary dysmenorrhea experience the reduced ability to concentrate, educational disruptions,^2^ and lower academic performance.^5^ The effects of primary dysmenorrhea-associated pain extend beyond individual women to society, resulting in regular work absenteeism.^5^

*Pathophysiology of primary dysmenorrhea.* The pathogenesis of primary dysmenorrhea has been linked to abnormally elevated prostaglandin secretion.^1, 6^ Abnormally high prostaglandin levels cause frequent and dysrhythmic uterine contractions, resulting in ischemia and hypoxia, which are considered to be major contributors to primary dysmenorrhea-associated pain.^1, 7^ Aetiological studies have reported that prostaglandin production is regulated by progesterone with prostaglandins and progesterone displaying an inverse relationship.^1, 6, 8^

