***Pilot trial***: We conducted a pilot trial to examine the effects of HIAT on plasma biomarkers that have been implicated in the pathophysiology of primary dysmenorrhea. The pilot trial findings indicated a trend towards increased progesterone levels (***d*** = 0.36) and decreased levels of prostaglandin F2 alpha (PGF2α) metabolites (***d*** = 0.35) in the HIAT group compared with those in the control group, which suggested that aerobic exercise may affect primary dysmenorrhea pain through effects on these mediators.^8, 13^

Because our research has supported the beneficial effects of HIAT, and a recent pilot study suggested a link between HIAT and progesterone and prostaglandin levels, the proposed randomised, controlled cross-over trial will test the following three hypotheses: (1) HIAT for 12 weeks will lead to significant reductions in pain intensity and absenteeism and improve academic performance compared to baseline levels; (2) pain improvements will be mediated by increased progesterone levels, resulting in decreased PGF2α levels; (3) HIAT will display superior cost-effectiveness compared with usual care (Wait-list control [WLC]) for primary dysmenorrhea treatment.

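### The Hypothesis 2 mediation model contains no treatment term and reverses the stated order of progesterone and PGF2α, so its decision rule does not require any effect of HIAT

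*Protocol*

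**What the plan says.** The hypothesis in the Background is that "pain improvements will be mediated by increased progesterone levels, resulting in decreased PGF2α levels". The Scientific premises section attributes the rise in progesterone to high-intensity exercise. The pathophysiology paragraph fixes the order of the two mediators: "prostaglandin production is regulated by progesterone with prostaglandins and progesterone displaying an inverse relationship". The stated chain is therefore HIAT, then progesterone, then PGF2α, then pain.

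Under Statistical tests and anticipated results, Hypothesis 2, the declared target is: "The mediation effects of increased progesterone levels on pain will be assessed using the Sobel test". The regressions are:

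- Step 1: "In Step 1, the regression coefficient between prostaglandin levels and pain (Path C) will be estimated".
- Step 2: "In Step 2, the regression coefficient between progesterone and prostaglandin levels (Path A) will be estimated".
- Step 3: "In Step 3, the regression coefficient between pain and prostaglandin levels, along with the mediator, progesterone levels (Path B), will be evaluated".
- Step 4: a Sobel test of the product AB, run with a named online calculator.

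Hypothesis 2 counts as supported if the Sobel p-value is below 0.05. No other condition is attached.

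**The concern.** A claim that a treatment effect is mediated needs the treatment in the model. None of the four steps contains HIAT, group or period, so the same analysis could be run on women of whom none had exercised, and it could still meet the support rule. The randomised contrast plays no part in the Hypothesis 2 decision.

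The order is also turned round. Step 1 makes prostaglandin the predictor of pain and Step 3 calls progesterone the mediator. The tested path is prostaglandin to progesterone to pain, whereas the Background and the Scientific premises put progesterone upstream of prostaglandin.

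This is not a detail left for an SAP. The protocol itself fixes the variables, the paths, the test and the decision rule, and an SAP that follows it would inherit the fault. Hypothesis 2 is one of three named hypotheses, its mediators are labelled primary, and its sample size sets the enrolment of 130.

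**Working it through.** **Stated chain against planned model**

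| Element | Stated hypothesis | Planned model |
|---|---|---|
| Exposure | HIAT | Prostaglandin |
| Mediator(s) | Progesterone, then PGF2α | Progesterone |
| Outcome | Pain | Pain |
| Treatment term | Required | None |

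**What the Sobel statistic responds to.** The usual form is z = AB / √(B²SA² + A²SB²), which equals 1 / √(1/tA² + 1/tB²) in absolute value, with tA = A/SA and tB = B/SB. It depends only on the two t-ratios. Path A is a simple regression of two variables, so its t-ratio is the same whichever is regressed on the other. What matters is which coefficient in Step 3 is Path B.

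**Inputs.** From the protocol: 130 enrolled, 30% attrition (130 × 0.7 = 91 completers), 100 required for Hypothesis 2 before drop-out, and d = 0.36 for progesterone. Assumed, because the protocol gives no values: standardised progesterone–PGF2α and PGF2α–pain paths of equal size p (negative and positive respectively), one measurement per woman, and a two-sided 5% test.

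**Reading 1: Path B is the prostaglandin coefficient; HIAT does nothing.** With purely serial biology, |A| = |B| = p, SA² = (1 − p²)/n and SB² = 1/n. The expected size of z is about p²/(p√((2 − p²)/n)) = p√(n/(2 − p²)). No treatment effect enters this expression.

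- n = 91, p = 0.3: 0.3 × √(91/1.91) = 2.07
- n = 91, p = 0.5: 0.5 × √(91/1.75) = 3.61
- n = 130, p = 0.3: 0.3 × √(130/1.91) = 2.48

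These are already above 1.96. Simulation with n = 91 gives support in 45.6%, 88.0% and 99.1% of trials for p = 0.3, 0.4 and 0.5. With n = 130 the range is about 73% to 100%.

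**Reading 2: Path B is the progesterone coefficient, as labelled.** If PGF2α carries the whole progesterone effect, the progesterone coefficient given PGF2α is zero, so AB = A × 0 = 0.

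- Chain true, HIAT effect on progesterone d = 0.36: support in 2.7% and 3.9% (n = 91, p = 0.4 and 0.5), and in 3.3% and 4.0% (n = 100 and 130, p = 0.5).
- Chain true, HIAT effect 0.8 SD and links of 0.7: 5.1% and 5.2% (n = 100 and 130).
- HIAT null, serial biology only: 1.4% to 4.4% (n = 91), so there is no excess false support here.
- HIAT null, progesterone–PGF2α path 0.5, PGF2α–pain path 0.3, plus a direct progesterone–pain coefficient of 0.3: 70% and 83% (n = 100 and 130). With an unmeasured common cause of progesterone and pain (loading 0.5) instead: 37% and 50%.

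**Serial model with group as the exposure (n = 100 / 130).** HIAT null: support in at most 5.0% in the scenarios run. Chain true, d = 0.36, p = 0.5: joint significance of the three paths 42% / 54%; delta-method test of the product 28% / 43%.

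**The case against.** The strongest objection is that the two failures belong to different readings. A reader might infer that one and the same test both produces false support and misses a true chain under the stated biology. The figures do not show that. On the prostaglandin reading a true chain is found in at least 99.6% of trials (p = 0.5, n = 100 or 130). On the labelled reading, false support stays at about 4% or less unless progesterone relates to pain beyond PGF2α. This objection stands, and each failure has to be tied to its reading.

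The zero coefficient in Reading 2 also needs PGF2α to carry the whole effect and to be measured without error. The protocol states a chain but does not exclude a direct path. That condition stands too.

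The percentages depend on path values that the protocol does not give, and on one observation per woman where the design has T1, T2 and T3. The 91 completers can be disputed as well: missing values are to be replaced with group means under intention to treat, which would give 130 analysed. Hence both sizes are shown. None of this touches the structural point.

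Two stronger inferences are not supported:

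- That Hypothesis 2 would be left wholly unexamined. The three regressions bear on the later links of the chain, and the sample size section plans for a difference in progesterone. The fault is that the support rule does not call on any HIAT effect.
- That the standard error will be computed wrongly because the printed expression shows no square root. The protocol names an online calculator as the tool, and a radical sign is easily lost in document conversion. Nothing shows that such an error would be made.

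**Conclusion.** The concern holds in this form. The planned model omits the randomised treatment from every step and reverses the order of the mediators stated elsewhere in the protocol, and no other section repairs either fault. A Sobel p below 0.05 would therefore not show that an effect of HIAT on pain is mediated, and a p above 0.05 would not count against it.

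The size depends on the reading of Path B. With Path B as the prostaglandin coefficient, false support under a null HIAT effect is about 45% to 99% with 91 women and about 73% to 100% with 130, for assumed paths of 0.3 to 0.5. With Path B as labelled, a true and fully serial chain is supported in about 1% to 5%, and false support needs an association of progesterone with pain beyond PGF2α. The omission of treatment is a fault on either reading and rests on no assumed number.

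**What to change.** Replace the four steps with a serial mediation model on the T2 parallel-group comparison, each equation adjusted for T1 values:

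1. progesterone on randomised group;
2. PGF2α on group and progesterone;
3. pain on group, progesterone and PGF2α.

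The indirect effect is the product of the group coefficient in (1), the progesterone coefficient in (2) and the PGF2α coefficient in (3). Declare Hypothesis 2 supported only if this product differs from zero in the hypothesised direction, for example by a bootstrap 95% confidence interval that resamples participants. Joint significance of the three paths is an acceptable alternative. If both periods are to be used, fit a mixed model with treatment, period and participant terms. Regressing within-participant differences on HIAT does not work, because in differences the treatment effect becomes the intercept.

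This changes analysis text only and needs no new data, assuming the mediators are measured at T2 with the other outcomes. The cost is candour about power: at d = 0.36, with assumed paths of 0.5 and before any gain from T1 adjustment, it is roughly 28% to 54% with 100 to 130 women, and lower if the paths are weaker. Hypothesis 2 should be described accordingly, for example as exploratory. The links from progesterone to PGF2α and from PGF2α to pain also remain observational, since only group is randomised.
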